#### Sample Size

2.11.1

Sample size and statistical power will be estimated using a Bayesian group sequential design, incorporating an interim assessment at 70% of enrolment [54]. The primary endpoint of the study will be defined as the comparison of remission rates between the TAU and rTMS groups and the TAU *vs*. VR-COG groups.

Literature convincingly supports the efficacy of TMS in major depressive disorder, although not specific to the oncological setting. A recent meta-analysis reported a significant effect on the remission endpoint of rTMS, with an odds ratio of 2.56 (95% CI: 1.73-3.78) [11], corresponding to a risk ratio of 1.5 (95% CI: 1.4-1.6). While no estimate is available on the efficacy of VR-based interventions comparable to VR-COG. Virtual reality-based interventions that do not include cognitive rehabilitation, within oncological settings, have shown effects with a standardized mean difference (SMD) in depressive symptom reduction of -1.11 (95% CI: -3.17 to 0.96) [15]. Considering that traditional (non-VR-based) cognitive rehabilitation for patients with depression, outside of oncology, is associated with a more modest reduction in depressive symptoms (SMD = 0.43; 95% CI: 0.17 to 0.70) [12], a conservative estimate of the effect size would be appropriate. Therefore, an SMD of 0.90, also corresponding to a risk ratio (RR) of 1.5, will be adopted. This design will be explored through a Monte Carlo simulation experiment with 10,000 runs. Each simulation run will assume a scenario with a different combination of effect size and sample size. For each scenario, the proportion of simulated trials correctly identifying at least one effective intervention will be computed, thereby estimating the empirical power of the study in a Bayesian context (Fig. **3**). Specifically, in each run, trial data will be generated under various scenarios assuming a remission rate of 0.6 for the TAU group and a risk ratio (RR) for comparisons with the experimental groups ranging between 1.4 and 1.6 (Fig. **3**). In the simulations, the total sample size n will vary from 50 to 170 patients, with increments of 10 subjects per simulation. The TAU and VR-COG groups will be assigned a sample size twice that of the rTMS group. For example, in a study with 50 participants, 10 patients would be assigned to the rTMS group (available only in Cagliari), 20 to the VR-COG group (Cagliari and Ferrara), and 20 to the TAU group (Cagliari and Ferrara).

For each Monte Carlo iteration, simulated trial data will be generated assuming a binomial distribution for the TAU group, xTAU ∼ Bin(n1 = 1/5 * n,p1 = 0.6), while for the other groups, the distribution will be xVR-COG ∼ Bin(n = 2/5 * n,p2 = 0.6 * RR). Within each iteration, the posterior probability for the RR will be computed using a beta-binomial distribution with a non-informative prior Beta (1,1). This approach has been chosen to keep the study design conservative during the planning phase. The posterior probability estimates for the RR will be obtained by taking the ratio of the posterior estimates of the remission rates between the two intervention arms (*e.g.*, VR-COG *vs*. TAU and rTMS *vs*. TAU).

Using these posterior estimates of the RR, it will be possible to derive the probability that the RR is greater than 1, applying the efficacy boundary method. This approach would allow for the definition of criteria to declare the intervention effective either at the end of the trial or earlier, at the time of interim analyses. The boundaries will be derived from the cumulative distribution function of a normal distribution, based on the frequentist O’Brien and Fleming boundaries, and translated into a Bayesian framework, as suggested in the literature [55]. The efficacy thresholds will be as follows: φ interim/(z=2.8)=0.997 e φ overall/(z=1.98)=0.976.

An interim analysis is planned at 70% of the total enrolment. If the posterior probability of the intervention’s efficacy exceeds the predefined efficacy boundary at the interim analysis, early termination of that intervention arm for efficacy will be considered. A total sample size of 100 participants (70 at interim analysis, allocated as 14 to rTMS, 28 to TAU, and 28 to VR-COG) would allow for a 41% probability of declaring the intervention effective at interim, assuming a risk ratio of at least 1.5. The evaluation of the other intervention will continue until the completion of the planned enrollment.

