### Statistical Analysis

2.11

The baseline data will be summarised as percentage (absolute numbers) for qualitative variables and median (1^st^ and 3^rd^ quartiles) for continuous variables. The group sequential Bayesian design [49] will be used to analyze the study's primary endpoints. Additionally, the first interim analysis will be carried out when 70% of enrolment is reached. The pattern chosen for the evaluation of the risk ratios of the primary endpoint will be defined by a beta-binomial model [50]. Apart from that, a SHELF (Sheffield Elicitation Framework) elicitation paradigm [51] will be used to define the prior probability of remission in the three intervention groups. The elicitation procedure will be carried out using R Shelf software [52]. Non-informative priors will still be used for sensitivity analyses. Upon reaching the interim, the probability that the posterior RR (relative risk) estimates, for the TAU *versus* rTMS or TAU *versus* VR-COG comparison, imply a value greater than 1 and surpass an efficacy boundary established in the interim, will be calculated. If at least one posterior probability for comparison using informative and non-informative priors exceeds the interim boundaries, then the trial will end due to efficacy; otherwise, the trial will continue until the end of the study. If the trial advances, the posterior probabilities for the RRs, with 95% confidence intervals, will be calculated. The intervention will be considered effective if the posterior probability that the RR exceeds 1 is higher than the ultimate effectiveness boundary. Secondary analyses will be performed using generalized Bayesian models by taking into account the interventions as a covariate and reporting 95% posterior confidence intervals. The convergence of the models will be evaluated using trace plots and Gelman statistics. The data will be analysed with an intention-to-treat approach and imputation of missing data according to a Last Observation Carried Forward (LOCF) protocol [53].

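### The O'Brien-Fleming thresholds fit a look at 50% information, not the planned 70%, and the look is tied to enrolment rather than to 3-month outcomes

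*Protocol article*

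**What the plan says.** The Sample Size section describes the boundaries as "based on the frequentist O’Brien and Fleming boundaries, and translated into a Bayesian framework" and prints them as "φ interim/(z=2.8)=0.997 e φ overall/(z=1.98)=0.976". On timing the same section says "An interim analysis is planned at 70% of the total enrolment", and the Statistical Analysis section says "the first interim analysis will be carried out when 70% of enrolment is reached". Oversight and Monitoring repeats the 70% figure.

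The interim sample is given as "70 at interim analysis, allocated as 14 to rTMS, 28 to TAU, and 28 to VR-COG", and the design is said to offer a "41% probability of declaring the intervention effective at interim, assuming a risk ratio of at least 1.5". The simulation behind this is run "assuming a remission rate of 0.6 for the TAU group", with Beta(1,1) priors.

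Under Evaluation Tools and Evaluation Timeline, the HAM-D-17 is taken at baseline, at 3 months (T1), and 3 and 6 months after T1. The Statistical Analysis section adds an intention-to-treat analysis with LOCF for missing data. The text does not say which visit defines remission at the look, nor that the look waits for any visit.

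**The concern.** An O'Brien-Fleming boundary depends on the fraction of information available at the look. The article fixes the method, the timing and the numerical thresholds, and the three do not agree. A later analysis plan would not remove the conflict, because the numbers are printed here.

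The trigger raises a second question. Remission cannot be known before T1, so on the day of the 70th enrolment everyone who entered in the preceding 3 months has no outcome. The 41% counts all 70. It is also attached to an unnamed intervention, although the two comparisons differ in size (28 against 28, and 14 against 28).

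This is the efficacy stopping rule. If its thresholds contradict its timing and its data cut is open, the decision at the look will have to be improvised.

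**Working it through.** **Inputs from the article.** Thresholds z=2.8 and 1.98; look at 70%; 28 TAU, 28 VR-COG and 14 rTMS at the look (40, 40 and 20 at the end); TAU remission 0.6; risk ratio 1.5, so 0.6 × 1.5 = 0.9; Beta(1,1) priors; first outcome at 3 months.

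**Assumptions.** One-sided level 0.025, which the printed values imply; steady accrual of 100 patients over A months, because the text gives no accrual rate and the Gantt chart is not shown.

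**1. The stated 41%.** Normal approximation, VR-COG against TAU, 28 per arm:
- Standard error under no difference: √(0.75 × 0.25 × 2/28) = 0.1157.
- Standard error under the alternative: √((0.24 + 0.09)/28) = 0.1086.
- Power: Φ((0.30 − 2.8 × 0.1157)/0.1086) = Φ(−0.221) = 41.2%.

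Exact beta-binomial enumeration gives 42.6% at Φ(2.8) = 0.99744 and 44.8% at the rounded 0.997. The 41% is therefore reproduced for VR-COG. For rTMS (14 against 28) the exact figures are 18.0% and 21.0%; for at least one arm, 47.9% and 50.3%. Taking TAU as one fifth of the total, as in the printed binomial formula, gives 26.2% per comparison and 36.0% for either, so the 41% does not come from that version.

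**2. The boundaries.** Classical two-look O'Brien-Fleming sets z₁ = C/√t and z₂ = C, with C solved so that the chance of crossing either is 0.025 (bivariate normal, correlation √t).

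| Information at the look | z interim | z final |
|---|---|---|
| 50%, classical | 2.797 | 1.977 |
| 70%, classical | 2.400 | 2.008 |
| 70%, O'Brien-Fleming-type spending (0.00738 spent at the look) | 2.438 | 2.000 |
| Printed | 2.8 | 1.98 |

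The ratio gives the same answer whatever the level: 2.8/1.98 = 1.414 = 1/√0.5, whereas a 70% look needs 1/√0.7 = 1.195.

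**3. Effect of the mismatch, all 70 with outcomes.**
- Used at 70%, the printed pair spends 0.0242 one-sided per comparison, below 0.025.
- Simulated chance of at least one false positive: about 4.7% as printed and 4.5% with the spending boundary.
- Final power for VR-COG: about 89% either way.
- Interim crossing for VR-COG: 43–45% as printed, about 60% with either 70% boundary. At least one arm: 48–50% against 65–67%.

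**4. Effect of the trigger.** If the look is taken at the 70th enrolment and only participants with T1 count, the number available is 70 − 3 × 100/A.

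| A (months) | With T1 | VR-COG v TAU | Interim crossing, printed threshold |
|---|---|---|---|
| 12 | 45 | 18 v 18 | 19–22% |
| 18 | 53 | 21 v 21 | 28% |
| 24 | 57.5 | 23 v 23 | 34% |
| 36 | 62 | 25 v 25 | 37–40% |

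The ranges reflect Φ(2.8) against 0.997.

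**5. If LOCF is applied at the look.** Participants without T1 carry baseline forward. Entry requires HAM-D-17 of at least 14, so they would in practice count as non-remitters. With equal numbers missing per arm, VR-COG crossing falls to about 2%, 5%, 9–11% and 19–22% for the same four accrual periods.

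**The case against.** The strongest reply is that the printed thresholds do no harm. They were fixed in advance, they are described only as based on O'Brien-Fleming, and a stricter interim boundary protects the error rate. That stands as far as validity goes. A reader might infer that type I error is inflated because the final 1.98 is slightly below the 2.00–2.01 that a 70% look needs. It is not: the stricter interim threshold more than pays for it, and the article's claim of under 5% false positives holds.

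A reader might also infer that the wrong boundary makes the 41% wrong. It does not. The figure agrees with the printed z=2.8 at 28 against 28; a 70% boundary would be a different design with a figure near 60%.

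Nor would the look come before any outcomes exist. Only participants from the last 3 months lack T1; in the scenarios above, 45 to 62 of the 70 have it. The interim sample of 70 could also be read as 70 analysed participants, with enrolment as shorthand. That reading is possible, but no sentence states it.

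Finally, the two halves of the point do not add up in full. With 45 to 53 outcomes the information is about one half, where 2.8 and 1.98 are about right. This is fair. Which half applies depends on the data cut, and the article leaves that open.

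What does not stand is the defence that the pair was chosen to be conservative. The article says so of the prior, not of the boundaries, and the values match a half-way look to rounding.

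**Conclusion.** The point holds in this limited form. The printed thresholds belong to a look at 50% information and contradict the planned 70%. The consequence is a loss of about 15 percentage points in the chance that VR-COG crosses at the interim (43–45% instead of about 60%), under TAU remission of 0.6, a risk ratio of 1.5 and complete outcomes for 70. Error control and final power are essentially unaffected.

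The 41% is sound for VR-COG if all 70 have outcomes, and does not describe rTMS. It is not reached if the look is taken at the 70th enrolment without waiting for T1. The shortfall depends wholly on accrual: large at 12 months, small at 36, and larger in every case if LOCF counts the missing as non-remitters.

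This should be corrected before the look is taken, but it does not undermine the final analysis.

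**What to change.** - Trigger the look when 70 randomized participants have T1 HAM-D-17 data, and say so wherever the 70% appears.
- Set both boundaries with an O'Brien-Fleming-type spending function at the information actually available. At exactly 70% the posterior thresholds are 0.9926 (interim) and 0.9773 (final). If the present pair is kept on purpose, say that it is stricter than O'Brien-Fleming at 70% and why.
- Rerun the simulation and state the interim probability separately for VR-COG and rTMS.

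The cost is two thresholds, one trigger sentence and a rerun. The drawback is a look about 3 months later. Under the same accrual assumption, 70 + 3 × 100/A patients would by then be enrolled: 95 at 12 months, about 78 at 36. A later look saves fewer patients, and the investigators should weigh that when they decide whether to keep it.

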#### Dissemination of Results

2.11.2

The dissemination committee will be formed with representatives from both units. The committee will be chaired by the principal investigator from unit 1, who will be responsible for the final decisions regarding the communication of the trial results to participants, healthcare professionals, the public, and other relevant groups (*e.g.*, through publications, reporting in databases, or other sharing data agreements), indicating any possible restrictions on publication. The guidelines for authorship will follow the principles of the 2019 Recommendations for the Conduct, Reporting, Editing, and Publication of Scholarly Work in Medical Journals drawn up by the ICMJE [56].

#### Registration

2.11.3

The trial is registered at ClinicalTrials.gov with ID NCT06589544.

## RESULTS AND DISCUSSION

3

Many people with cancer experience psychological issues, like depression. This could make it more difficult to cope with the burden of their illness, lower treatment acceptance, increase hospital stays, lower quality of life, and increase the risk of suicide [1, 5]. The detection of depression in cancer patients is challenging. Depression can easily be overlooked because symptoms of cancer and its treatment resemble neurovegetative symptoms of depression, such as fatigue, loss of appetite, and sleep disturbance.

Evaluating the feasibility and the cost-effectiveness of nonpharmacological interventions for cancer patients' quality of life and depressive symptoms, cognitive function, and other depression-related conditions is one of the main goals of this study. In this RCT, we will specifically compare standard TAU with rTMS and VR-COG *versus* TAU alone. The assessment of the cognitive functioning, depression-related conditions, and cost-effectiveness of the interventions under consideration will be another crucial aspect. The results of this study will allow us to obtain knowledge that can be translated into clinical practice regarding the feasibility and cost-effectiveness of an innovative therapeutic approach aimed at the treatment of depression in individuals suffering from oncological pathologies. This will have practical implications for the clinical health systems, considering the high costs linked to oncological diseases and depressive disorders. Despite this, the financial costs associated with depression are also substantial in patients with cancer. Cancer patients with a diagnosis of depression have annual healthcare costs more than double those of non-depressed patients, with higher charges occurring in major healthcare categories of ambulatory care, emergency department charges, and inpatient hospital settings [3].

The findings of the present RCT will be able to guide further study and clinical decisions in terms of both choice of treatment and the personalization of the same. The study will ultimately favour the application of safe and non-invasive interventions for the population with oncological pathologies and depressive disorders. The monitoring of the cost-effectiveness of the program, including both the screening and intervention phases, will allow policymakers to be guided in the implementation of this evidence in routine clinical practice.

### Risk and Benefits

3.1

The use of immersive virtual reality (VR) may be associated with mild and transient side effects, including dizziness, nausea, headaches, visual fatigue, impaired limb coordination, diminished postural stability, a decreased sense of presence, and potentially inappropriate reactions to real-world environments. The side effects of rTMS are also mild and transient, and include headache, discomfort at the scalp stimulation site, tingling sensations or muscle twitching, and light-headedness. Nonetheless, significant adverse effects are not expected, as rTMS and VR are considered safe and well-tolerated procedures, with an extremely low risk of side effects [16, 57-60].

## STUDY LIMITATIONS

4

This study is strengthened by its methodologically sound feasibility randomized controlled design, the adoption of standardized virtual reality-based cognitive remediation and rTMS protocols, a comprehensive multimodal evaluation encompassing several psychosocial outcomes, and consistency with established frameworks for the development and testing of complex interventions.

Potential limitations include challenges in participant recruitment within an oncological population presenting with mild to moderate depressive symptoms. These challenges may stem from clinical instability related to ongoing treatments (*e.g*., chemotherapy-related fatigue, pain, or cognitive burden), fluctuating symptom severity, competing medical appointments, and reduced motivation or engagement associated with depressive symptomatology. Additionally, concerns about time commitment, physical discomfort, or unfamiliarity with technology-based interventions may further limit willingness to participate. Given its pilot nature, the study is not intended to demonstrate definitive clinical efficacy, but rather to provide exploratory evidence and guide the design of subsequent, adequately powered trials.

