### Study Design

2.1

The study will involve a randomized controlled trial (RCT) among persons with oncological diseases and mild-moderate depression. The study will include a longi-tudinal, three-arm design with participants assigned by randomization to either an active interventional protocol based on repetitive transcranial magnetic stimulation (rTMS) + treatment as usual (TAU) or virtual reality-based cognitive remediation (VR-COG) + TAU, and to a control setting, treatment as usual (TAU). The main outcomes are expected to show the superiority of each experimental intervention (rTMS + TAU or VR-COG +TAU) over the control condition (TAU). Participants will be randomized, independently, to parallel intervention groups in each of the two units [unit 1, Health Trust of Ferrara (UniFE), with 1:1:1 randomization to (a) TAU, (b) rTMS + TAU, and (c) VR-COG + TAU; unit 2, University Hospital of Cagliari (UniCA), with 1:1 randomization to (a) TAU and (b) VR-COG + TAU] with the stratification for the unit of the recruitment.

The timeline of the different study phases and the protocol flow diagram are presented in Figs. (**1** and **2**), respectively.

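### Section 4 calls the trial a pilot not meant to show definitive efficacy, but 2.1, 2.11 and 2.11.1 give it a superiority aim, a verdict of effectiveness and an early stop for efficacy; these must be reconciled

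*Protocol article*

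**What the plan says.** Two descriptions of the trial stand side by side in the protocol article.

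*Exploratory.* Section 4 (Study Limitations) gives the pilot nature of the study as the reason that "the study is not intended to demonstrate definitive clinical efficacy, but rather to provide exploratory evidence", and says the results will "guide the design of subsequent, adequately powered trials". The Introduction likewise calls the effectiveness to be measured preliminary, although it also describes a pragmatic trial of effectiveness.

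*Decision-making.* Section 2.1 (Study Design): "The main outcomes are expected to show the superiority of each experimental intervention". Section 2.11 (Statistical Analysis): "The intervention will be considered effective if the posterior probability that the RR exceeds 1 is higher than the ultimate effectiveness boundary". Section 2.11.1 (Sample Size) supplies boundaries of 0.997 at the interim and 0.976 at the end, a 41% chance of an interim declaration, a true positive rate of 81% and a false positive rate below 5%.

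The interim look at 70% of enrolment has two rules. In 2.11, when one comparison or more "exceeds the interim boundaries, then the trial will end due to efficacy; otherwise, the trial will continue until the end of the study". In 2.11.1, "early termination of that intervention arm for efficacy will be considered", and "The evaluation of the other intervention will continue until the completion of the planned enrollment".

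Section 2.3 (Outcomes) places feasibility beside depressive symptoms as primary. Quality of life, cognition and related conditions are secondary, and cost-effectiveness is tertiary. Section 2.4 measures the quality-of-life gain for cost-effectiveness from T0 to T3.

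**The concern.** A posterior probability above 0.976 would be a finding of effectiveness under 2.11 and exploratory evidence under section 4. Nothing in the article says which reading governs. Ending enrolment because efficacy has been reached treats the question as answered, whereas section 4 says that this study is not the one to answer it.

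The conflict also has a practical cost. A pilot exists largely to deliver feasibility data, which are primary here. Stopping for efficacy shortens that data collection, along with the secondary outcomes and the cost-effectiveness comparison. Under 2.11 it also ends the other experimental arm, whose own comparison may not have crossed.

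**Working it through.** **Inputs, all from 2.11.1 unless stated.** TAU remission 0.6; risk ratio (RR) 1.5, so 0.6 × 1.5 = 0.90 in an effective arm; Beta(1,1) priors; interim counts TAU 28, VR-COG 28, rTMS 14; final counts 40, 40, 20 (100 in a 2:2:1 ratio); interim boundary Φ(2.8) = 0.9974, printed as 0.997. The 20% dropout used in step 4 is my assumption.

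**1. The plan's 41%.** For each pair of remission counts, P(RR > 1) = P(θ_E > θ_TAU), with θ ~ Beta(1 + x, 1 + n − x). Summing the binomial probabilities of all pairs above the boundary gives:

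| Comparison at interim | Boundary Φ(2.8) | Boundary 0.997 |
|---|---|---|
| VR-COG vs TAU (28 vs 28) | 42.6% | 44.8% |
| rTMS vs TAU (14 vs 28) | 18.0% | 21.0% |

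The 41% is reproduced to within 2 points as the VR-COG comparison.

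**2. The trigger in 2.11, at least one crossing.** The two comparisons share the TAU arm, so this was simulated (200,000 runs). With RR 1.5 in both:
- Φ(2.8): 42.7% + 18.0% − 12.7% (both) = 48.0%
- 0.997: 44.7% + 21.0% − 15.4% = 50.3% (50.2% simulated directly; the difference is rounding)

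If only VR-COG works, the trigger is met in 43 to 45% of trials. If only rTMS works, it is met in 18 to 21%. If neither works, it is met in about 0.5%.

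**3. Enrolment lost after a crossing.**
- Whole-trial rule (2.11): 100 − 70 = 30 patients, or 30%; rTMS ends at 14 of 20.
- Arm-level rule (2.11.1), one arm crossing, places not reallocated: 40 − 28 = 12 if VR-COG stops, or 20 − 14 = 6 if rTMS stops.

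**4. Precision of a feasibility proportion.** Half-width = 1.96 × √(p(1 − p)/n), with p = 0.20:
- n = 100: 1.96 × √(0.16/100) = 7.8 points; n = 70: 9.4 points
- rTMS, n = 20: 17.5 points; n = 14: 21.0 points

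For any p, the overall widening factor is √(100/70) = 1.20.

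**5. Error rates.** The chance of at least one false declaration over both looks is 4.6 to 4.7%, consistent with the stated bound of 5%. The 81% was not reproduced: VR-COG alone gives 88.6 to 89.4%, rTMS alone about 71%, and either arm 93 to 94%. That is a separate matter. This point needs only the fact that the plan claims 81%.

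**The case against.** The best reply is that section 4 disclaims *definitive* efficacy, not any assessment of efficacy. A trial of 100 patients may apply a posterior decision rule and still call its answer preliminary. The Introduction makes preliminary effectiveness a primary aim, and the pilot language comes mainly from one passage on limitations. This stands in part. A reader might infer that the plan disowns every efficacy claim, and the text does not go that far. What remains unexplained is why enrolment should end for efficacy in a study whose result is exploratory, and why a design with a stated 81% true positive rate leaves adequate power to later trials.

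A reader might also infer that 30% of the data is lost whenever a boundary is crossed. The documents do not support that. The figure belongs to the rule in 2.11; under 2.11.1 the loss is 6 or 12 places. Nor does the 41 to 50% chance go with rTMS ending at 14 under 2.11.1, where rTMS stops only if rTMS itself crosses (18 to 21%). If recruitment continues while the 3-month outcomes mature, fewer than 30 patients are lost. If ending the trial also ends follow-up, more T3 data could go. The article does not say which.

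The measured harm is moderate. The overall half-width grows by 1.6 points at an assumed dropout rate, and the article gives no precision target that would be missed. The proportion recruited among eligible patients has a different denominator, so step 4 does not describe it. Cost-effectiveness is tertiary and should not be read as co-primary with feasibility.

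**Conclusion.** The concern holds in this form: section 4 and sections 2.1, 2.11 and 2.11.1 give different status to the same posterior result, and no text reconciles them. Both statuses are stated outright, so this is not detail left to an analysis plan.

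Under the plan's own assumptions, an efficacy stop is a likely event: 41% by its figure, and 48 to 50% for at least one comparison if both risk ratios are 1.5. Followed as written, 2.11 would then leave up to 30 of 100 patients unenrolled and reduce the precision of the primary feasibility outcome, the secondary outcomes and the tertiary cost-effectiveness comparison. Under 2.11.1 the loss is 6 or 12 places.

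These probabilities rest on TAU remission of 0.6, Beta(1,1) priors and an interim at exactly 28, 28 and 14 patients with outcomes known. Section 2.11 also applies elicited priors, which are not given, so their effect on the chance of stopping cannot be calculated. The conflict affects interpretation and precision; it does not invalidate the trial.

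**What to change.** Give the remission analysis one status throughout.

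- **If it is a pilot:** remove the early stop for efficacy from 2.11 and 2.11.1, enrol the planned 100, and report the posterior probabilities as preliminary, without a verdict of effectiveness. Bring the superiority sentence in 2.1 into line. The cost is giving up a possible early stop; no patients beyond the planned 100 are needed.
- **If a superiority test is meant:** remove from section 4 the pilot wording and the reference to later adequately powered trials, and remove the preliminary wording from the Introduction. Reconcile the stopping rules in 2.11 and 2.11.1 so that a crossing in one arm ends neither the other arm nor the follow-up for feasibility and cost. Deleting the disclaimer alone would leave the data loss as it is. Even with the rules reconciled, an arm that stops early still gives up its 6 or 12 places.

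Either option is a change of protocol wording.
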